#### Program Theory

A program theory explains how a program is expected to work and under what conditions [10]. The Data Health program theory (Multimedia Appendix 1) is captured in a series of “if-then” statements and is based on key findings from the pilot test, published literature reporting trial results or theoretical abstractions [8,16,27,50-53], and the research group’s experiences and previous research in the field [20,54-57]. Mechanisms of change are the hypothesized causal links between the program components and identified outcomes, triggered within the contexts in which the program is implemented [10]. In total, we hypothesize 6 mechanisms of change as plausible causal links between the data-driven approach and the GMB process and outcomes; these are indicated by mechanisms connected to steps 2 and 3 in Figure 3. To understand the interactions among context, program components, mechanisms, and outcomes; the research group visualized the initial program theory as a systems map, illustrated in Figure 3. The map summarizes our proposed model of how program components are expected to lead to systems change and outcomes. The connecting arrows show how changes in one part of the system are expected to generate changes in other parts of the system. The Data Health program theory and system map will continually be refined and revised as part of the evaluation process.

**Figure 3 figure3:**
[figure not shown]
The Data Health system map.

#### Process Evaluation (RQ1)

In the process evaluation [58], we will examine whether the data-driven approach and the GMB process (steps 2 and 3 of the program) are being implemented as intended, the associated contextual factors and the mechanisms of change.

Both quantitative and qualitative methods will be used to collect data for the process evaluation (Table 1). Following the Medical Research Council guidelines [58], 5 process evaluation components will be assessed: recruitment, reach, fidelity, dose delivered, and dose received. In addition, we will examine whether the 6 hypothesized mechanisms of change are activated and the extent to which these mechanisms are modified through their interaction with contextual factors. However, we will remain open to other emerging mechanisms.

**Table 1 table1:** Items, methods, instruments, and frameworks used in evaluation of implementation (research questions 1-3).

Component and items of interest			Methods and data	Applied evaluation instruments and frameworks
**Process evaluation—steps 2 and 3 of the program**				
	**Context information**			
		Examples: School type School size School location School and municipal structure	Semistructured interviews with the principal school managers and the municipal program coordinators (after GMB^a^3) Facts obtained through school and municipality websites	Medical Research Council guidance [58]
	**Implementation**			
		What is delivered: Recruitment Reach Fidelity Dose Adaptations	Registration of participants during meetings and GMB sessions Exit surveys to all participants (after data presentation meetings, GMB2 and GMB3), semistructured interviews with the school program coordinators (after GMB2) and the principal managers (after GMB3)	Medical Research Council guidance [58] COMPACT Stakeholder-driven Community Diffusion Survey [59]
	**Mechanisms of change**			
		Knowledge of health promotion Shared understanding of health issues Motivation and engagement Collaboration Shared decision-making Resource allocation Other emerging mechanisms	Exit surveys to all participants (after data presentation meetings, GMB2 and GMB3), semistructured interviews with the school program coordinators (after GMB2) and the principal managers (after GMB3)	Medical Research Council guidance [58] COMPACT Stakeholder-driven community diffusion survey [59]
**Implementation of actions—step 4 of the program**				
	**Actions**			
		Number of actions initiated Primary variable of influence Action level (beliefs, goals structures, events)	Semistructured interviews with the school and municipal program coordinators quarterly	The Systems Thinking in Community Knowledge Exchange computer software [45] Action Scale Model [27]
	**Involvement**			
		Number of involved participants Level of involvement in preparation, execution, and implementation of the developed actions	Semistructured interviews with the school and municipal program coordinators quarterly	The involvement matrix [53]
	**Unintended consequences**			
		Rippling effects and potential positive and negative unintended consequences of the actions implemented	The community of practice network will be involved in a process (meetings or workshops) of identifying the rippling effects	Ripple effect mapping [60]
**Program normalization—steps 1 and 5 of the program**				
	**Maintenance of collaboratives**			
		Potentials, barriers and needs Partnership synergy	Notes from the meetings for program maintenance (6 months after GMB3) Semistructured interviews with the school manager (after GMB3) and the municipal program coordinator managers (6 months after GMB3)	Partnership synergy [51]
	**Program normalization**			
		Coherence Cognitive participation Collective action Reflexive monitoring	Semistructured interviews with the school manager (after GMB3) and the municipal program coordinator managers (6 months after GMB3)	Normalization process theory framework [61]

^a^GMB: Group Model Building.

Qualitative and quantitative data will be interpreted separately and combined. Quantitative data will be analyzed descriptively, whereas qualitative interviews will be recorded, transcribed, and thematically analyzed in NVivo (Lumivero) [60].

#### Implementation of Actions (RQ2)

Actions initiated by the school, municipal, or community actors and the consequences of these actions are a direct indicator of systems change. The number of actions initiated and the primary factors in the locally developed CLD that are influenced will be tracked and visually added to the CLD. The Action Scale Model [27] will be used to determine whether the actions address one of four hierarchical levels to change the functioning of the system in the anticipated direction: (1) beliefs (eg, the school creates a local action group as health promotion champions), (2) goals (eg, the school sets new goals for health promotion), (3) structures (eg, school and municipal staff receive training on the complexity of health), and (4) events (eg, a single sport event at schools) [27]. The hierarchical structure suggests that changing beliefs and goals will not only have a greater systemic impact but also be more costly and time consuming than implementing single events [27]. We will also examine which participants (ie, students, school staff and management, municipal staff, and community actors) are involved in the planning and implementation of the actions and how and to what extent they are involved. The involvement levels of the participant groups will be interpreted using the involvement matrix [53].

All actions and involvement will be tracked on a quarterly basis for up to 2 years after GMB3 through semistructured interviews with the school and municipal program coordinators and involved community actors to enable interpretation of the level of system change and engagement across participant groups over time (Table 1).

In addition, an adapted version of “ripple effect mapping” [62] will be used to understand the rippling-initiated actions, effects, and potential positive and negative unintended consequences of the actions implemented. The CoP will be involved in a process to explore and visualize unintended consequences.

#### Program Normalization (RQ3)

We will explore the opportunities, barriers, and what is needed to integrate the collaboratives and the program into normalized practice (steps 1 and 5 of the program).

The school-municipality collaboration and program normalization will be explored through interviews with school and municipal program coordinators (Table 1). Interview guides inspired by the Partnership Synergy framework [51] will be developed to explore the functioning of the collaborations and the potential for maintenance, and the normalization process theory [61] will be used as a framework for understanding program normalization. In addition, carefully written notes will be taken from the program maintenance meetings, which will be completed as part of step 5 of the program.

Interviews will be recorded and transcribed, and all data will be analyzed thematically in NVivo [60] to understand opportunities, barriers, and needs related to sustaining collaborations and normalizing the program. Finally, we will develop recommendations for the implementation of systems approaches for sustainable health promotion in vocational schools.

#### Organizational Outcomes (RQ4)

School organizational readiness to address health promotion is selected as a primary organizational outcome. We will apply the “organizational readiness framework” [50] to track change over time. Organizational readiness refers to the extent to which an organization is willing and able to implement change, and the elements in the framework have previously been shown to be related to implementation success [63]. School organizational readiness will be assessed by questionnaires administered to all school staff, supplemented by semistructured interviews with the principal managers at the schools (Table 2).

**Table 2 table2:** Items, methods, instruments, and frameworks used in evaluation of effectiveness (research questions 4 and 5).

Component and items of interest				Methods and data		Applied evaluation instruments and frameworks
**System outcomes**						
	**Organizational readiness**					
		Baseline and change in the following: Organizational motivation General capacity Health promotion capacity	Questionnaire to staff members (4 times in total) Semistructured interviews with principal managers (after GMB^a^3)		Organizational readiness [50]	
**Individual outcomes**						
	**Health behavior**					
		Baseline and changes in the following: Mental health and well-being Physical activity Food intake Nicotine use Alcohol use	Questionnaire to all students (4 times in total)		WHO-5^b^ [64] and SGPALS^c^ [65] Validated measures from the Danish National Health Survey and the Health Behaviour in School-aged Children study [66]	
	**Health promotion outcomes**					
		Baseline and changes in the following: Health literacy Knowledge relevant to the problem of interest Self-empowerment Self-confidence Self-efficacy Behavioral intentions Motivation Social network and interaction Social connectedness Student autonomy	Questionnaire to all students (4 times in total)		HLQ^d^ [67]; HLSAC^e^ [68] validated measures from the Danish National Health Survey and the Health Behaviour in School-aged Children study [66]	

^a^GMB: Group Model Building.

^b^WHO-5: World Health Organization (Five) Well-Being Index.

^c^SGPALS: Saltin-Grimby Physical Activity Level Scale.

^d^HLQ: Health Literacy Questionnaire.

^e^HLSAC: Health Literacy for School-Aged Children.

The questionnaire instrument will adapt and refine existing and tested items [20,69] across 3 dimensions and 10 subdimensions: motivation (relative advantage, compatibility, complexity, and priority), general capacity (culture, climate, and staff capacity), and program-specific capacity (knowledge, skills, and abilities). We will use exploratory and confirmatory factor analyses to initially validate the instrument and assess its internal consistency and convergent validity. The questionnaire will be distributed electronically via email in SurveyXact [70] to all school staff (eg, teachers, counselors, and administrators), and repeated data will be collected 4 times during the study period (Figure 2). Changes in school organizational readiness will be assessed primarily using linear mixed modeling, adjusting for clustering, with school as a random effect and time as a fixed effect.

Interviews with school leaders will contribute to a deeper understanding of how the support and priorities of the school management can stimulate or hinder the school’s readiness and willingness to change. The interviews will be recorded, transcribed, and analyzed thematically according to the dimensions and subdimensions of organizational readiness.

To generate a comprehensive understanding of school organizational readiness, a convergent parallel mixed methods design will be used in the analyses [71]. Quantitative and qualitative data will be analyzed independently and then compared, related, and interpreted.

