We will examine preliminary effectiveness (see descriptions of organizational outcomes [RQ4] and individual outcomes [RQ5]) at the organizational level (ie, school organizational readiness) and at the individual level (ie, students’ health behavior and well-being) using a quasi-experimental design with a nonrandomized clustered stepped-wedge strategy. The 8 program schools will be enrolled in 2 steps, matched by educational track (one school from each main track) and geographic location (2 schools from 2 Danish regions). The matched clusters will be assigned to early start (January 2022) or late start (6 months later). This design allows for a sequential roll-out of the program and allows us to control for differences between study sites (vertical control) and secular trends (horizontal control) during the study period [49]. Organizational- and individual-level data will be collected simultaneously at all 8 schools 4 times during the 2-year study period at baseline and at 3 follow-up points (T1, T2, and T3; Figure 2). As systems change takes time to diffuse into individual behavior changes [31], the research team will in due course seek opportunities and funding for longer-term data collection (ie, a 5- and 10-year follow-up).

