Most analyses will be based on cross-sectional data and descriptive in nature, interpreting the mean differences between the intervention and control groups. However, the analyses will also include linear mixed models with time and selected covariates (eg, gender, age, ethnicity, and socioeconomic status) as fixed effects and school as a random effect. It is important to note that the total time of 2 years to assess individual outcomes may be too short to provide conclusive evidence at this level.

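### The staff and student mixed models name school as the only random effect, so their standard errors for change are unreliable, in a direction the protocol gives no means of predicting

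*Protocol article*

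**What the plan says.** Under Organizational Outcomes (RQ4): "School organizational readiness to address health promotion is selected as a primary organizational outcome". The questionnaire goes by email "to all school staff (eg, teachers, counselors, and administrators), and repeated data will be collected 4 times during the study period". Change is assessed primarily by "linear mixed modeling, adjusting for clustering, with school as a random effect and time as a fixed effect".

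Under Individual Outcomes (RQ5), most student analyses are described as cross-sectional and descriptive. Linear mixed models are also planned, with time and selected covariates "as fixed effects and school as a random effect".

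Under Study Design, effectiveness is examined "using a quasi-experimental design with a nonrandomized clustered stepped-wedge strategy". Eight schools enter in two steps six months apart, matched by educational track and region. "Organizational- and individual-level data will be collected simultaneously at all 8 schools 4 times during the 2-year study period".

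Under Strengths and Limitations (Program Evaluation), each site chooses its own health issue, actions and route to normalization. The caveat there about mostly cross-sectional data concerns students, not staff.

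**The concern.** Taken in its ordinary sense, a school random effect is a random intercept: each school has its own level, constant over the four waves. The design departs from this in two ways.

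- **School-by-wave variation.** Schools choose different issues and actions, so their means should move differently between waves. A constant school effect assigns all such movement to individual-level residual noise, which is then divided by the number of answers. The standard error of a change, or of an early-versus-late contrast, comes out too small.
- **Repeated staff.** All staff are approached at every wave, so some will presumably answer more than once. A person's stable level cancels out of their own change, but the model counts it as noise in both waves. The standard error of change comes out too large.

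Readiness is the primary organizational outcome, and the stated aim is to inform whether national scale-up can be recommended. Intervals whose error has unknown size and sign are a poor basis for that.

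**Working it through.** The protocol gives no sample size, ICC, variance, number of staff, staff overlap or alpha, so there is no figure of its own to reproduce. The check shows how the named model behaves over assumed ranges.

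**Notation.** Total variance is 1. ICC is the between-school share at one wave, and s is the fraction of it that is stable over time, so school-by-wave variance is d = ICC × (1 − s). There are m answers per school and wave. ρ is the within-person correlation, with every person answering each wave. For the variance of a school-wave mean, as it enters a change:

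- true ≈ (1 − ICC)(1 − ρ)/m + d
- reported by the school-intercept model ≈ (1 − ICC + d)/m
- k = reported SE / true SE = square root of reported/true
- rejection rate of a nominal 5% z-test ≈ 2 × [1 − Φ(1.96k)]

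**Students (ρ = 0).** From Individual Outcomes (RQ5), about 2000 students and 90% completion give m = 2000 × 0.9 / 8 = 225. This is a ceiling, because the 90% applies to students present in class. The value m = 75 is an assumed lower case.

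| m | ICC | s | true | reported | k | rejection |
|---|---|---|---|---|---|---|
| 225 | 0.05 | 0.80 | 0.95/225 + 0.010 = 0.0142 | 0.96/225 = 0.0043 | 0.55 (SE understated 1.83 times) | 28% |
| 225 | 0.02 | 0.95 | 0.98/225 + 0.001 = 0.00536 | 0.981/225 = 0.00436 | 0.90 (1.11 times) | 7.7% |
| 75 | 0.05 | 0.80 | 0.95/75 + 0.010 = 0.0227 | 0.96/75 = 0.0128 | 0.75 (1.33 times) | 14% |
| 75 | 0.02 | 0.95 | 0.98/75 + 0.001 = 0.0141 | 0.981/75 = 0.0131 | 0.96 (1.04 times) | 6% |

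A simulation of 20,000 runs with 4 versus 4 schools agrees: 7.6% to 28.4% at m = 225 and 5.7% to 13.9% at m = 75.

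**Staff, repetition alone (d = 0).** With full overlap, the SE of change is overstated by about 1/√(1 − ρ): 1.29 at ρ = 0.4 and 1.83 at ρ = 0.7. If only a share p of staff answer both waves, this becomes about 1/√(1 − pρ). At p = 0.5 it is 1/√0.80 = 1.12 to 1/√0.65 = 1.24.

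**Staff, both features together.** The named model was fitted by REML to simulated null data: 8 schools, 4 waves, 20 or 50 staff per school, full overlap, 800 runs per setting, and a normal reference. Two contrasts were tested: last wave minus baseline, and an added program indicator. The second assumes early schools are exposed from wave 2 and late schools from wave 3, because Figure 2 is not available.

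| Setting | k | rejection |
|---|---|---|
| Benchmark: s = 1, ρ = 0 | 0.96–1.04 | 3.7–6.5% |
| Repetition only: s = 1, ρ = 0.6 | 1.54–1.58 | 0–0.6% |
| Drift only: ICC 0.05, s = 0.8, ρ = 0 | 0.79–0.95 | 6.1–12.5% |
| Drift only: ICC 0.05–0.10, s = 0.5, ρ = 0 | 0.51–0.83 | 11.6–33.3% |
| Both: 20 staff, ICC 0.05, s = 0.8, ρ = 0.6 | 1.24–1.28 | 0.9–1.1% |
| Both: 50 staff, ICC 0.05, s = 0.8, ρ = 0.6 | 1.02–1.07 | 3.7–4.8% |
| Both: 50 staff, ICC 0.10, s = 0.8, ρ = 0.6 | 0.80–0.82 | 9.6–12.0% |
| Both: 50 staff, ICC 0.10, s = 0.5, ρ = 0.6 | 0.57 | 25.9–28.7% |

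The formula reproduces these. For 50 staff, ICC 0.05, s = 0.8: true 0.95 × 0.4/50 + 0.010 = 0.0176, reported 0.96/50 = 0.0192, k = 1.04. For 50 staff, ICC 0.10, s = 0.5: true 0.90 × 0.4/50 + 0.050 = 0.0572, reported 0.95/50 = 0.0190, k = 0.58.

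**School-level analysis, same data.** A t-test on the 8 school changes from baseline to last wave (7 df) rejected 4.0% to 7.0%. An early-versus-late comparison of changes from wave 1 to wave 2 (6 df) rejected 3.9% to 6.5%. Monte Carlo error is about 0.8 points. The mixed model with added school-by-wave and staff effects was not itself simulated.

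**The case against.** The document is a condensed article. One sentence naming school need not be the complete covariance structure, and it does not use the word intercept. Person effects, school-by-period terms and degrees-of-freedom methods are often left to an analysis plan. That is fair as far as completeness goes. But the article does specify a model for its primary organizational outcome, and the structure it names does not match the data it describes. This therefore concerns a stated model and not only a missing detail.

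A reader might infer that the intervals are always too narrow and that false positives follow. The documents do not support this. For staff the two omissions oppose each other, in some settings they cancel, and nothing in the protocol says which dominates.

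A reader might also take it as given that the same staff answer all four times and can be linked, through the email distribution or the key files. The protocol states neither a linked panel nor the extent of overlap, and it names staff turnover as a challenge. The 1.29 to 1.83 overstatement is therefore an upper range that requires full overlap.

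For students, the protocol itself calls most analyses descriptive, labels effectiveness preliminary, warns that two years may be too short, and states no alpha. This lowers the stakes, but it does not correct the standard errors of the mixed models that are planned. The same cross-sectional caveat removes the case for a repeat-student effect.

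**Conclusion.** The point holds in a limited form. With school as the only random effect, standard errors for change and for any program contrast cannot be relied on, because the model ignores school-by-wave movement in 8 schools and correlation between a staff member's repeated answers.

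For staff, with both features present and the assumed values above (20 or 50 staff per school, ICC 0.05 or 0.10, stability 0.5 or 0.8, within-person correlation 0.6, full overlap), actual type I error runs from about 1% to 29%, passing through settings where it is close to 5%. The net direction is unknown. For students, where repetition matters little, the error is toward intervals that are too narrow: about 8% to 28% at the ceiling of 225 answers per school and wave, and 6% to 14% at 75, given ICC 0.02 to 0.05 and 80% to 95% stability. All of these inputs except the 225 are assumptions.

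This should be corrected before analysis. It does not show that any particular interval will be too narrow or too wide.

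**What to change.** - Add a school-by-wave random effect to both the staff and the student model, with a small-sample correction such as Kenward-Roger. Alternatively, analyse school-level changes in the 8 schools.
- If school-level changes are used, respect the matching by track and region. An unpaired early-versus-late t-test on 6 df ignores it. Pairing schools by track gives 4 pairs and 4 − 1 = 3 df, so the choice should be made in advance.
- State whether staff answers can be linked across waves. Add a staff random intercept only if they can. If not, the school-by-wave effect or the school-level analysis still gives a usable standard error for change.
- Leave out a random effect for repeat students, since most student data are cross-sectional.

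The cost is a few lines of model code and no new data. Intervals for the program effect may widen, and with 8 schools they may be wide.

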### Program Evaluation

#### Research Questions

In total, 5 RQs will comprise the evaluation of the Data Health program:

RQ1 (process evaluation—steps 2 and 3 of the program): To what extent is the data-driven approach and the GMB process implemented as intended, and what seem to be the most important mechanisms of change and contextual factors?RQ2 (implementation of actions—step 4 of the program): What characterizes the planned and initiated actions and what are the unintended consequences related to implementation? Who is involved in the planning and implementation?RQ3 (program normalization—step 1 and 5 of the program): What are the opportunities, barriers, and needs for the collaboratives and program to be sustained and normalized?RQ4 (organizational outcomes): Does the program stimulate organizational changes in schools to work in a more health-promoting direction?RQ5 (individual outcomes): Does the program contribute to improvement in health behaviors and well-being among vocational students?

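### The primary RQ4 mixed model, and secondarily the RQ5 mixed model, name no program-exposure or early/late group-by-time term, so their time coefficients mix secular trend with program effect

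*Protocol article*

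**What the plan says.** Under Study Design, the protocol article evaluates organizational and individual outcomes "using a quasi-experimental design with a nonrandomized clustered stepped-wedge strategy". The 8 schools enter in two steps, an early start in January 2022 and a late start 6 months afterwards. On measurement it says: "Organizational- and individual-level data will be collected simultaneously at all 8 schools 4 times during the 2-year study period". The stated benefit of the roll-out is that it "allows us to control for differences between study sites (vertical control) and secular trends (horizontal control) during the study period".

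Under Research Questions, RQ4 is a question about the program: "Does the program stimulate organizational changes in schools to work in a more health-promoting direction". RQ5 likewise asks whether the program contributes to better student behavior and well-being.

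Under Organizational Outcomes (RQ4), in the text after Table 2, change in readiness is to be assessed primarily by "linear mixed modeling, adjusting for clustering, with school as a random effect and time as a fixed effect". No between-group comparison is stated for RQ4.

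Under Individual Outcomes (RQ5), most analyses are to be cross-sectional and descriptive, interpreting differences in means between intervention and control groups. Mixed models are planned in addition, specified as follows: "linear mixed models with time and selected covariates (eg, gender, age, ethnicity, and socioeconomic status) as fixed effects and school as a random effect".

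**The concern.** A stepped wedge separates program effect from calendar trend only if the analysis contains both: calendar time, and which schools had started the program at each wave (or, equivalently, how the early and late groups diverge). Both stated models contain the first and not the second. The staggered start is therefore not used, and the trend control claimed under Study Design is not delivered.

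At stake is the meaning of the main quantitative RQ4 result. If readiness drifts upward in all schools for unrelated reasons, the stated model reports that drift as change, and a reader will credit the program. If the program works, the model reports trend plus a partly diluted effect. Effectiveness is called preliminary, but under Objectives the evaluation is meant to inform whether national scale-up can be recommended.

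**Working it through.** The article states no sample size, power or effect figure, so there is nothing of its own to reproduce. The check is whether the program effect can be recovered from the stated terms.

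**Inputs from the document:** 8 schools, two start groups (taken as 4 + 4), 4 simultaneous waves (baseline, T1, T2, T3), late start 6 months after early start.

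**Assumptions:** the timing of the waves relative to the starts is in Figure 2, which is not shown, so three schedules were tried (0 = not started, 1 = started, over the four waves). Trend (0.1 per wave) and program effect (0.3) are illustrative.

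**Step 1: what the time-only model estimates.** With balanced data, the wave contrast against baseline has expectation

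trend at wave t + (share of schools exposed at t) × effect.

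For schedule A below, with trend and effect both present:
- T1: 0.1 + 0.5 × 0.3 = 0.25
- T2: 0.2 + 1 × 0.3 = 0.50
- T3: 0.3 + 1 × 0.3 = 0.60

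Nothing in the model splits these sums.

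**Step 2: linear time slope**, Σ(t − 1.5) × mean at t ÷ 5, for t = 0 to 3.

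| Schedule | Early | Late | Trend 0.1, effect 0 | Trend 0, effect 0.3 |
|---|---|---|---|---|
| A | 0111 | 0011 | 0.100 | (−0.5×0.15 + 0.5×0.30 + 1.5×0.30)/5 = 0.105 |
| B | 0111 | 0001 | 0.100 | (−0.5×0.15 + 0.5×0.15 + 1.5×0.30)/5 = 0.090 |
| C | 0011 | 0001 | 0.100 | (0.5×0.15 + 1.5×0.30)/5 = 0.105 |

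Pure drift and a pure program effect give nearly the same coefficient.

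**Step 3: add a 0/1 exposure term** to school and time. Under A, B and C the design is of full rank. An effect of 0.3 is returned as 0.3 and an effect of 0 as 0, with or without trend.

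**Step 4: small simulation** (200 runs, schedule A, assumed 30 respondents per school and wave, intraclass correlation 0.05, trend 0.1 SD per wave, no program effect). The linear time term in the time-only model was significant in 95.5% of runs. The exposure term, fitted with categorical wave, was significant in 6.5%, within Monte Carlo error of 5% (√(0.05 × 0.95/200) = 1.5 points).

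**Step 5: limits of the remedy.**
- *Growing effect.* Let d1, d2, d3 be the effects after one, two and three exposed waves. Under schedule A the early-minus-late differences are 0, d1, d2 − d1, d3 − d2, and a single constant exposure term estimates d1 − (d3 − d1)/3. For effects 1, 2, 3 that is 1 − 2/3 = 0.33.
- *Time-since-start coding.* Write D0 to D3 for the observed early-minus-late differences. Then d1 = D1 − D0, d2 = D1 + D2 − 2D0, d3 = D1 + D2 + D3 − 3D0. With equal independent variances these have variances in ratio 2 : 6 : 12, so the standard error of d3 is √(12/2) ≈ 2.4 times that of d1. The estimates d2 and d3 also require equal effects in the two start groups.
- *Late start before T1.* If waves were evenly spaced from January 2022 (24/3 = 8 months apart, an assumption), the late start at 6 months would precede T1. Both groups would then be 0111, and a 0/1 exposure term would be completely aliased with wave.

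**The case against.** The strongest reply is that this is a condensed article: one sentence per model describes how clustering and time are handled, the design section makes the early and late groups clear, and exposure coding could sit in an analysis plan. Coding can indeed be left there. But the RQ4 sentence names the model's random and fixed effects, and the term that carries the research question is not among them. Reading time as time since program start does not help, because calendar time is then missing and trend is again uncontrolled.

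A reader might infer that no RQ5 analysis can show a program effect. The document does not support that. Its main RQ5 analyses are descriptive intervention–control comparisons, and the covariate list of the mixed model is open, although every example is a personal characteristic. What remains is that these comparisons are unadjusted, involve nonrandomized schools, and have an untreated comparator only until the late schools start.

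A reader might also size the bias from the rise in overweight in the Introduction (30% in 2014 to 39% in 2019). Overweight is not among the outcomes in Table 2, so that figure describes no RQ4 or RQ5 result.

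Nor do the documents make school fixed effects obligatory. Schools are matched by track and region, and fixed versus random school effects is partly a modelling preference. The preliminary status of the effectiveness evaluation, the manager interviews in RQ4 and the caution that 2 years may be too short all limit the weight of the results. They do not change what the time coefficient measures.

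**Conclusion.** The point holds, most strongly for RQ4. Followed as written, the primary RQ4 model cannot answer its question, because its only fixed effect combines secular trend with the average program effect. The same is true of the RQ5 mixed model, but not of every RQ5 analysis.

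The confounding follows from the listed terms and does not depend on the assumed numbers. Its size in this trial cannot be given: the near-equal slopes (0.100 against 0.090 to 0.105) and the 95.5% rejection rate illustrate assumed trends, effects, respondent numbers and wave timings. Whether a simple exposure term identifies the effect depends on when the late start falls relative to T1, which the available text does not settle.

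**What to change.** In both mixed models, enter wave as a categorical fixed effect and add a program-exposure term by school and wave, or an early/late group-by-wave term. Report the exposure term as the program effect and the wave coefficients as secular trend only. State the exposure status of each start group at each wave, so that identification can be checked.

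If the late start precedes T1, use the group-by-wave contrast, since 0/1 exposure is then aliased with wave. That contrast reflects the earlier group's extra exposure time, because no school is untreated at any follow-up, and it should be described so.

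Study Design expects effects to take time to diffuse, so add time-since-start coding as a sensitivity analysis. School fixed effects can be added in the same way, given the nonrandomized start order.

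The cost is a sentence or two per model and no new data. Confidence intervals will be wider than under the time-only model, markedly so for later exposure periods (about 2.4 times the standard error for the third period against the first under schedule A), where the estimates also rest on equal effects in the two start groups.
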